### Independent Variables of the Study

This study considers demographic and environmental factors as independent variables. Demographic variables include gender, age, education level, occupation, and socioeconomic status (SES). Respondents’ SES will be measured based on ownership of durable assets such as a television, refrigerator, car, electricity, telephone, and radio; the number of bedrooms; and home infrastructure conditions such as access to drinking water sources and the presence of water channels around the house [68]. Using principal component analysis, respondents’ SES will be categorized into 5 quantiles ranging from the lowest (quantile 1) to the highest (quantile 5) [69]. Environmental variables in the study include the location of the residence, categorized as rice fields, coastal areas, or hilly areas, and accessibility to villages, classified as easy, moderate, or difficult to access. Additionally, the study considered proximity to health facilities, including the type and distance of the nearest health facilities. For secondary data from the health center, patient records from 2013 to 2023 were reviewed for all patients with suspected malaria, and positive or negative cases were confirmed based on laboratory examination results. The number of malaria cases based on gender, age group, type of *Plasmodium*, time (year and month), location of residence, and type of treatment and the number of deaths since the period under review were collected from the 4 selected health centers.

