The seventh outcome variable in this study is variation in access to basic drinking water and its associated factors among rural communities in ENT Province, Indonesia. Household access to basic drinking water is defined based on the WHO Joint Monitoring Program guidelines, which classify water sources into 4 categories: no service, unimproved, limited, and basic [75]. To analyze this variable, a dichotomous classification will be used, where households will be categorized as either having access to an improved drinking water source (Yes=1) or lacking access to an improved drinking water source (No=0). This classification will help determine disparities in access to safe drinking water and identify key factors influencing these differences.

The secondary outcomes of this study are derived from the analysis of patient medical records from 4 selected health centers, along with additional data from the Department of Health, East Sumba District. The eighth outcome variable focuses on the monthly number of malaria cases recorded over the past 10 years, from 2013 to 2023. By integrating data from both health centers and the Meteorological Agency of East Sumba, this study aims to explore the impact of climatic variables on malaria case fluctuations in this region, following the methodology of a previous study [76]. This analysis will provide valuable insights into seasonal and long-term trends in malaria transmission, which could help inform future malaria prevention and control strategies.

The ninth outcome variable in this study examines the demographic variations in malaria prevalence among communities residing in hilly and coastal areas over the past 10 years (2013-2023). Among the 4 selected health centers, Baing and Nggongi Public Health centers are located in coastal areas, whereas Mahu and Kananggar Public Health Centers are situated in hilly regions. Given that vector distribution and species composition may vary between different geographic settings [77], previous studies in Indonesia have reported significant differences in malaria prevalence between coastal and hilly areas [78]. By analyzing malaria case records from these health centers, this study aims to assess regional disparities in malaria burden and determine how demographic and environmental factors contribute to these differences. This information may help tailor malaria prevention and control efforts to the specific needs of different geographic regions.

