For the ninth outcome variable, malaria cases records from 2013 to 2023 will be analyzed across different geographic areas. Data from Baing and Nggongi Public Health Centers, representing coastal regions, will be combined, while records from Mahu and Kananggar Public Health Centers, representing hilly areas, will be aggregated separately. Malaria prevalence will be calculated on a monthly, yearly, and cumulative basis over the study period. To visualize the demographic trends, malaria prevalence will be plotted against key demographic variables. The disparity of malaria prevalence in demographic variables will be investigated using a chi-square test [10,82].

For the tenth outcome variable, descriptive statistics will be used to calculate frequencies and percentages of overall malaria prevalence and trends in malaria transmission considering variations by season, month, year, sex, age, and species of malaria parasite. Epidemiological characteristics, including age group, sex, and *Plasmodium* species–adjusted malaria-related mortality rates in East Sumba District will be presented as percentages followed by their 95% confidence intervals. Chi-square tests will be used to compare the associations of malaria burden by age groups and sex. The malaria prevalence and mortality rate will be illustrated in a map to assess the distributions of the cases geographically [79,80].

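### The ninth outcome sets out to explain coastal-hilly differences in malaria burden, but its stated analysis neither adjusts the terrain contrast for patient mix nor includes any explanatory environmental factor

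*Protocol article*

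**What the plan says.** Under Outcome Variables, the ninth outcome is introduced as a description of demographic variation in malaria prevalence in hilly and coastal communities, 2013 to 2023. The same paragraph then widens the purpose. Case records are to be used to assess regional disparities and to "determine how demographic and environmental factors contribute to these differences", so that control efforts can be fitted to each type of area.

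The matching paragraph under Statistical Analysis has four steps:

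- **Grouping.** "Data from Baing and Nggongi Public Health Centers, representing coastal regions, will be combined". The two hilly centers form a second, separate group.
- **Summary.** Prevalence is calculated monthly, yearly and cumulatively.
- **Display.** Prevalence is graphed by demographic characteristic.
- **Test.** "The disparity of malaria prevalence in demographic variables will be investigated using a chi-square test".

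No regression, standardisation or stratified method is named for this outcome. For each of the first seven outcomes the same section names a binary logistic regression.

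Independent Variables of the Study gives this definition: "Environmental variables in the study include the location of the residence, categorized as rice fields, coastal areas, or hilly areas". The items it lists as taken from the health-center records are gender, age group, parasite type, year and month, residence location, treatment and deaths. Residence location is the only environmental item among them.

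**The concern.** Asking how factors contribute to a difference between two areas is a question about explanation. A chi-square test of malaria status against age or sex shows whether burden varies by age or sex. It does not show whether that variation accounts for the gap between coast and hills. For that, terrain and demographics have to be considered together.

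If the stated steps are all that is done, a coastal-hilly gap produced by a different age or sex mix could be reported as a geographic effect, or a real geographic difference could be hidden by opposing mixes. Since the stated use is to tailor control by area, a crude comparison could point that advice the wrong way. The environmental half of the aim has no analysis behind it, because terrain cannot serve both as the difference to be explained and as its explanation.

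**Working it through.** The article states no sample size, prevalence or effect size for this outcome, so there is no figure to reproduce. The check compares aim with analysis, then uses two illustrations. **All numerical inputs below are assumed; none comes from the article.**

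**Step 1. Aim against analysis.**

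| Part of the aim | Stated analysis |
|---|---|
| Regional disparity | Terrains aggregated separately, prevalence by period; no test or estimate of the terrain difference named |
| Demographic contribution | Plots and chi-square on demographic variables; no terrain contrast adjusted for them |
| Environmental contribution | None beyond terrain itself |

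**Step 2. A gap due to age mix alone.** Assume positivity of 30% in children and 15% in adults in both terrains. Let children be 60% of coastal and 40% of hilly records.

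- Crude positivity = (share of children × 30%) + (share of adults × 15%)
- Coastal: 0.6 × 0.30 + 0.4 × 0.15 = 0.24
- Hilly: 0.4 × 0.30 + 0.6 × 0.15 = 0.21
- Crude odds ratio: (0.24/0.76) / (0.21/0.79) = 1.19
- Standardised to half children, half adults: 0.5 × 0.30 + 0.5 × 0.15 = 22.5% in both terrains

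The 3-point gap disappears once age is held equal.

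**Step 3. What pooled chi-square tests can distinguish.** Assume 5000 people per terrain and two scenarios, shown as cases/total.

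| | Coastal children | Coastal adults | Hilly children | Hilly adults |
|---|---|---|---|---|
| A: age mix only | 600/3000 (20%) | 100/2000 (5%) | 400/2000 (20%) | 150/3000 (5%) |
| B: terrain only | 560/2500 (22.4%) | 140/2500 (5.6%) | 440/2500 (17.6%) | 110/2500 (4.4%) |

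In both scenarios the margins are 1000/5000 children and 250/5000 adults, and 700/5000 coastal (14%) and 550/5000 hilly (11%). Pearson chi-square is N(ad − bc)² / (product of the four margins), and the denominator is 5000 × 5000 × 1250 × 8750 each time.

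- Age, pooled over terrain: 10,000 × (1000 × 4750 − 4000 × 250)² / denominator = 514.3 in A and in B
- Terrain, pooled over age: 10,000 × (700 × 4450 − 4300 × 550)² / denominator = 20.6 in A and in B

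The pooled tests are identical although the causes are opposite. A logistic model with terrain and age separates them: the age-adjusted coastal odds ratio is 1.00 (95% CI 0.88 to 1.13) in A and 1.34 (1.18 to 1.51) in B.

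**Step 4. Limit of any model here.** Each terrain is represented by two health centers. Terrain is therefore confounded with whatever else distinguishes those centers, such as access, testing or recording. Adjustment can address patient mix but cannot isolate particular environmental causes.

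**The case against.** The best defence is that the outcome is first defined as demographic variation in prevalence, which a chi-square on demographic variables does address, and that the sentence on contributions is a broad statement of motive. That lowers the importance. The sentence still names demographic and environmental contributions as something the study will determine, and the analysis paragraph is specific enough to show that it will not.

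A reader might also infer stronger criticisms, which the article does not support:

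- **That no environmental variable is used.** By the article's own definition, coastal or hilly residence is environmental, and it is the grouping factor. What is absent is an environmental variable that could explain the contrast.
- **That the terrains are not compared.** They are aggregated separately, so a side-by-side description is implied. What is absent is a formal estimate.
- **That calendar time is ignored.** Monthly and yearly prevalence is planned. What is absent is adjustment of the terrain contrast for time.
- **That the planned tables could never reveal an age-mix effect.** Step 3 holds for tables pooled over terrain, and the article does not say whether they will be. Split by terrain, the Step 2 inputs would show 30% against 30% in children and 15% against 15% in adults. Standardisation would then be easy, but it is not planned.
- **That climate data in hand could fill the gap.** Meteorological data are foreseen for the eighth outcome, but the article does not say they have been obtained. Nor does it list population denominators by age, sex and terrain among the items collected.

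Finally, the article condenses a fuller plan. That would excuse missing detail, but here the aim and the method are both stated and do not match.

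**Conclusion.** The mismatch stands in a limited form. As written, the plan describes prevalence by terrain and tests demographic variables without adjustment. It does not adjust the coastal-hilly contrast for age, sex or calendar time, and it leaves the environmental part of the aim unanalysed. The size of any distortion cannot be derived from the article; the 24% against 21% example shows only that moderate differences in age mix are enough to create a gap.

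Importance is minor. The outcome is one of three secondary ones, rests on records from 2013 to 2023 that predate the campaign, and does not enter any estimate of the intervention effect.

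**What to change.** Keep the descriptive prevalence tables and plots, and add one adjusted analysis.

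- **Model.** Among the suspected-case records that the article says were reviewed, with positive and negative results confirmed by laboratory, fit a logistic regression of positivity on terrain, age group, sex, year and season. Report the terrain odds ratio before and after demographic adjustment, with 95% confidence intervals. State that it describes these four centers and that it concerns positivity among suspected cases rather than community prevalence.
- **Simpler alternative.** Report age- and sex-standardised positivity by terrain.
- **Wording.** Remove environmental factors from the aim sentence, since two centers per terrain cannot isolate specific environmental causes.

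Both analyses assume that age group, sex and date were extracted for the negative records as well as the positive ones. The article lists these items for malaria cases, so this should be confirmed first. If they were not extracted, the aim should be narrowed to describing demographic patterns by terrain. The cost is a little more analysis and a narrower stated aim.

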### Statistical Analysis

All statistical analyses will be conducted using SPSS version 27 (IBM Corp), and *P* values <.05 will be considered statistically significant.

For the first outcome variable, descriptive statistics will be used to summarize participants’ sociodemographic characteristics and environmental variables including gender, age group, SES, education level, family size, distance to the nearest health facilities, village accessibility, and household location. A chi-square test will be applied within each study group (intervention and control) to evaluate the association of basic malaria understanding, basic malaria knowledge, the level of malaria knowledge, and the level of malaria awareness before and after the intervention. Unpaired sample *t* tests will be used to investigate the statistical differences. Comparisons will be performed within groups (pre- and postintervention) and between groups to determine the impact of the intervention [61]. Furthermore, a binary logistic regression model will be used to identify the potential factors associated with malaria awareness in both the intervention and control groups [39].

For the second outcome variables, descriptive statistics will be used to summarize participants’ sociodemographic and environmental characteristics including gender, age group, SES, education level, family size, distance to the nearest health facilities, access to village, and household location for both study groups. A chi-square test will be used to evaluate the association between AMTSB and the sociodemographic and environmental characteristics of participants. Unpaired samples *t* tests will be used to assess the statistical differences. Comparisons will be conducted within and between groups for both pre- and postintervention periods. Moreover, binary logistic regression analysis will be used to identify predictors associated with AMTSB among participants in both study groups [41]. Only predictors that demonstrate statistically significant differences (*P*<.05) will be retained in the final model.

For the third variable response, participants’ sociodemographic characteristics and environmental variables in each group will be reported using descriptive statistics. The association between a good level of MPMK with predictors will be investigated using a chi-square test. Unpaired samples *t* tests will be used to investigate the statistical differences. Comparisons will be conducted within and between groups for both pre- and post-intervention periods. Furthermore, binary logistic regression analysis will be performed to identify key risk factors influencing MPMK [44,81] among rural communities in both study groups.

For the fourth outcome variable, descriptive statistics will be used to summarize participants’ sociodemographic characteristics and environmental variables based on the awareness that malaria can be prevented. Associations between bed net use and its predictors will be examined using a chi-square test. Binary logistic regression analysis will then be conducted to identify the primary risk factors associated with bed net use during the dry season among rural communities [71].

For the fifth outcome variable, participants’ sociodemographic characteristics, environmental variables, and malaria-related behavioral aspects in both the intervention and control groups will be analyzed. Data will be presented as proportions for each season (dry and wet seasons) to examine the seasonal variations in malaria prevention behaviors. The associations between bed net use and its predictors will be evaluated using a chi-square test for each season. The main risk factors for bed net use during the dry and wet seasons will be investigated using binary logistic regression analysis. The adjusted odds ratio will be used to quantify the strength of the associations between bed net use and its predictors in each season [71,72].

For the sixth outcome variable, participants’ sociodemographic characteristics, environmental variables, and behavioral aspects of malaria in each group will be reported using descriptive statistics. The association between a good level of MPMP and its predictors will be investigated using chi-square tests. Unpaired samples *t* tests will be used to investigate the statistical differences. Comparations will be performed within and between groups for both pre- and postintervention periods. Moreover, binary logistic regression analysis will be performed to identify the primary risk factors influencing MPMP [73,74] among rural communities in both study groups.

For the seventh outcome variables, descriptive statistics will be used to summarize participants’ sociodemographic characteristics, environmental variables, and malaria-related behaviors based on their source of drinking water. The associations between access to improved drinking water and its predictors will be assessed using chi-square tests. Furthermore, a binary logistic regression model will be used to determine predictors influencing access to improved drinking water [75].

For the eighth outcome variable, descriptive analyses of climatic factors across different subdistricts will be performed. Data will be aggregated at the subdistrict level, and statistical estimates will be generated for each variable. Specifically, the total number of malaria cases and the average malaria incidence will be computed. Climatic variables, including maximum, minimum, and mean temperature values, will be calculated. Moreover, data from all 22 subdistricts will be analyzed, focusing on malaria cases and climatic parameters, including maximum, minimum, and average temperature values. To depict the seasonal dynamics, seasonal variations in climatic parameters and malaria cases will be plotted, covering the 2 main seasons. A time series for both predictor and outcome variables will be plotted to deliver an overall perspective. A map of malaria cases will be generated. Scatterplots will be developed to illustrate relationships between malaria cases and predictor variables, following the methods of a previous study [76].

For the ninth outcome variable, malaria cases records from 2013 to 2023 will be analyzed across different geographic areas. Data from Baing and Nggongi Public Health Centers, representing coastal regions, will be combined, while records from Mahu and Kananggar Public Health Centers, representing hilly areas, will be aggregated separately. Malaria prevalence will be calculated on a monthly, yearly, and cumulative basis over the study period. To visualize the demographic trends, malaria prevalence will be plotted against key demographic variables. The disparity of malaria prevalence in demographic variables will be investigated using a chi-square test [10,82].

For the tenth outcome variable, descriptive statistics will be used to calculate frequencies and percentages of overall malaria prevalence and trends in malaria transmission considering variations by season, month, year, sex, age, and species of malaria parasite. Epidemiological characteristics, including age group, sex, and *Plasmodium* species–adjusted malaria-related mortality rates in East Sumba District will be presented as percentages followed by their 95% confidence intervals. Chi-square tests will be used to compare the associations of malaria burden by age groups and sex. The malaria prevalence and mortality rate will be illustrated in a map to assess the distributions of the cases geographically [79,80].

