### Study Design and Sampling Technique

This study used a cluster-assigned quasi-experimental design with pretest and posttest assessments in both control and intervention groups. The cluster unit for this study was the village, which was not randomized because the research team aimed to implement the intervention across all villages within a selected subdistrict, where the subdistrict leader would serve as a role model to encourage the community to improve malaria awareness. To obtain a representative sample, the research team randomly selected 4 of the 22 subdistricts, of which 2 were assigned as the intervention groups and 2 served as the control groups. The first 3 subdistricts each had 6 villages, and the fourth subdistrict had 7 villages; therefore, a total of 25 villages participated in the study, representing about 16% of all the villages in the district. Of these, 13 villages were assigned to the intervention group, while 12 villages formed the control group. The number of sampled households selected from each village was proportional to the number of households in that village. Within each selected village, households were randomly sampled to serve as an experimental unit as indicated in Figure 2.

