### Sample Size Calculation

To determine the required sample size for the baseline prevalence of study outcomes, the research team applied the Leslie-Kish formula for calculating the sample size in cross-sectional studies [66]:

where n_0_ is the initial sample size; p is the prevalence of malaria awareness in ENT Province (48.8%) [39], Z is the confidence level at 95% (standard value of 1.96), and d is the relative precision (0.05); therefore, the initial sample size was 384 participants. For the population survey, a community correction factor of 2 was applied, doubling the required sample size to 768 participants. Additionally, a 15% buffer was added to account for potential incomplete data, primarily due to nonresponse or failure to complete interviews. Thus, the final sample size was determined to be 884 participants with 442 individuals in the control group and 442 individuals in the intervention group. This number served as a guideline for recruiting participants for the household survey, which was conducted both before and after the intervention.

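### The campaign comparisons for outcomes 1, 2, 3 and 6 treat respondents as independent although two whole subdistricts were assigned against two, so between-group P values and confidence intervals will be too optimistic

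*Protocol article*

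**What the plan says.** Study Design and Sampling Technique describes the design: "This study used a cluster-assigned quasi-experimental design with pretest and posttest assessments in both control and intervention groups". It names the village as the cluster: "The cluster unit for this study was the village, which was not randomized". The allocation, however, was made one level higher. Four subdistricts were drawn at random, "of which 2 were assigned as the intervention groups and 2 served as the control groups". As a result "13 villages were assigned to the intervention group, while 12 villages formed the control group". The same section then says that "households were randomly sampled to serve as an experimental unit".

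Sample Size Calculation contains one step that may allow for clustering: "a community correction factor of 2 was applied, doubling the required sample size to 768 participants".

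Statistical Analysis fixes the methods outcome by outcome. For outcome 1 (awareness index), "A chi-square test will be applied within each study group (intervention and control) to evaluate the association of basic malaria understanding", knowledge and awareness before and after the campaign. Unpaired t tests follow, within and between groups, with the declared aim of determining the campaign's impact, and then a binary logistic regression. Outcomes 2 (appropriate treatment seeking), 3 (prevention knowledge) and 6 (prevention practice) also get unpaired t tests within and between groups and binary logistic regression. No random effect, generalised estimating equation, cluster-robust variance, survey-design correction or village-level summary is named. The limitations in the Discussion cover non-random allocation of villages and self-report, but not clustering.

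**The concern.** People in the same village share a health centre, terrain, leadership and exposure to the broadcasts, so their answers are likely to be correlated. Chi-square tests, unpaired t tests and ordinary logistic regression all assume independent respondents. In a between-group comparison of assigned clusters, any positive correlation makes the true standard error larger than the one these methods report. Ordinary differences between a few villages or subdistricts can then be declared campaign effects.

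A larger sample does not repair this. Doubling recruitment recovers precision, but the standard errors are still computed as if every respondent counted in full. This is also not a detail left for a later document, because the article itself names the test for each outcome. The results are meant to inform malaria policy in Indonesia, so a false claim of effect would matter.

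**Working it through.** **The article's own figure.** n0 = 1.96² × 0.488 × 0.512 / 0.05² = 383.9, rounded to 384. Then 384 × 2 = 768, and 768 × 1.15 = 883.2, rounded to 884, or 442 per group. The figure reproduces with d taken as 5 absolute percentage points.

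**Inputs.** 884 respondents, 25 villages and 4 subdistricts come from the article. That gives m = 884/25 = 35.4 per village and 884/4 = 221 per subdistrict. Alpha is 0.05, taken as two-sided. No ICC is given, so all ICCs below are assumptions.

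**Formulas for the between-group test.** Design effect DE = 1 + (m − 1) × ICC. True type I error of the respondent-level test = 2 × [1 − Φ(1.96/√DE)].

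**If the factor of 2 is a design effect.**
- Implied village ICC = (2 − 1)/(35.4 − 1) = 0.029.
- 1.96/√2 = 1.386, so the true type I error is 16.6%.
- Interval width relative to the correct one is 1/√2 = 0.71, so intervals are about 29% too narrow.
- Effective sample size is 442/2 = 221 per group.

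**Range for village clustering alone.** The simulated column is from 20,000 runs of the respondent-level chi-square test.

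| Village ICC | DE | True type I error | Simulated |
|---|---|---|---|
| 0.01 | 1.34 | 9.1% | 8.8% |
| 0.03 | 2.03 | 16.9% | 16.8% |
| 0.05 | 2.72 | 23.4% | 23.3% |

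**Subdistrict clustering.** With m = 221, a subdistrict ICC of 0.005 gives DE 2.10 and about 18% error. An ICC of 0.01 gives DE 3.20 and about 27% (simulated 26%).

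**Both levels together.** The simulation used 25 villages of 36, prevalence 48.8% and village ICC 0.029.
- Village clustering only: about 17% for the respondent-level test and about 5% for a village-level t test.
- With an assumed subdistrict ICC of 0.01 added: about 34% to 35% for the respondent-level test, and still about 16% for the village-level t test.

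**Interval half-width for a between-group difference near 48.8%.** The naive standard error is √(2 × 0.488 × 0.512/442) = 0.0336.
- Respondent level: 1.96 × 0.0336 = 6.6 points.
- Village level, ICC 0.03, 23 df: 2.069 × 0.0336 × √2.03 = 9.9 points.
- Subdistrict level, ICC 0.01, 4 − 2 = 2 df: 4.303 × 0.0336 × √3.20 = about 26 points.

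**Within-group pre-post test.** Here DE = 1 + (m − 1) × ICC − m × ICC × r, where r is the correlation of village effects between waves.
- ICC 0.01, r = 0.8: DE = 1 + 0.344 − 0.283 = 1.06, error 5.7%.
- ICC 0.05, r = 0.5: DE = 1 + 1.718 − 0.884 = 1.83, error 14.8%.
- r = 1: error 4.4% to 4.9%. The inflation vanishes once r exceeds 1 − 1/35.4 = 0.97.

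**The case against.** Several stronger readings are tempting, and the article does not support them.

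- *Every planned test is affected.* Outcome 8 is descriptive. Outcomes 9 and 10 use register data from 2013 to 2023, before the campaign. Outcomes 4, 5 and 7 plan associations with predictors, plus proportions by season for outcome 5, and no between-group t test. An explicit campaign comparison is planned only for outcomes 1, 2, 3 and 6.
- *The pre-post P values must be too small.* The chi-square test quoted above is a within-group test. Stable village effects largely cancel there, so its inflation is smaller and may be absent.
- *Re-interviewing people adds to the optimism.* Phase IV says only that respondents in the two waves may differ. If some are the same people, positive within-person correlation makes an unpaired pre-post test conservative.
- *The plan itself declares a design effect of 2.* It speaks of a community correction factor for a population survey and mentions neither clustering nor an ICC. The 17% and 29% figures depend on that reading.
- *All four subdistricts had a leader's recording.* Only the two intervention subdistricts did.

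The article also explains why whole subdistricts were used and admits possible selection bias. That is fair disclosure, but it concerns bias and leaves the standard errors uncorrected. The between-group tests for outcomes 1, 2, 3 and 6 have no such defence.

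**Conclusion.** The concern holds for the between-group campaign comparisons of outcomes 1, 2, 3 and 6. Their P values and confidence intervals will be too optimistic for any positive ICC. The direction is certain, but the size rests on ICCs that the article does not give. It is about 17% true type I error and intervals about 29% too narrow if the factor of 2 is a design effect. It is about 9% to 23% over assumed village ICCs of 0.01 to 0.05, and higher with any subdistrict variation.

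For within-group pre-post tests the error is about 6% to 15% at village level (ICC 0.01 to 0.05, between-wave correlation 0.5 to 0.8), and there is no inflation if village effects are almost perfectly stable.

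A reader might infer that adjusting for village fully solves the problem. It does not. With two subdistricts against two, subdistrict differences are confounded with the campaign. The point must be settled before the final analysis.

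**What to change.** 1. For outcomes 1, 2, 3 and 6, define the campaign effect as the between-group difference in pre-post change. Estimate it by comparing the 25 village-level changes, or by a mixed logistic model with village and village-by-period random effects and small-sample degrees of freedom. Include coastal or hilly setting as a fixed effect. The article places Baing and Nggongi on the coast and Mahu and Kananggar in the hills, and the campaign staff came from Baing and Mahu, so each group appears to have one of each.
2. Allow for village clustering in the logistic models of the other survey outcomes.
3. State that the assigned unit is the subdistrict, two against two, and show the four subdistrict-level changes.
4. State that village-level adjustment does not remove the confounding of the campaign with subdistrict differences, and word the conclusion accordingly.

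The cost is revised analysis text and some programming, using village and subdistrict identifiers. No new data are needed. The price is wider intervals and a more cautious conclusion. The timeline puts the final analysis between March 2025 and December 2026.
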